## Discussion

KOA patients often experience a variety of symptoms that interfere with their daily activities. There are four main symptoms, including pain, stiffness, reduced joint motion and muscle weakness [38], which are interrelated rather than independent of each other. Muscle weakness is a hallmark of KOA patients and a better predictor of disability than pain or narrowing of the joint gap [39]. Decreased muscle strength can reduce knee stabilizers and proprioception, increase the risk of falls and accelerate progression of degenerative KOA [8, 39]. Several studies have found that strengthening the quadriceps is effective in relieving knee pain, reducing joint mobility, and delaying KOA degeneration [9, 11, 12]. Therefore, pain relief is the primary demand to seek KOA treatment. Muscle strength could be the key to treating KOA-associated pain.

TC, as a kind of KOA exercise therapy, is widely considered to be a suitable exercise therapy for KOA patients. Significant improvements have been reported in pain, muscle strength, physical function, balance, mental health and other arthritic symptoms [25, 40]. Some researchers also believe TC activates neuroendocrine and autonomic nervous functions, secretes neurochemicals, triggers an analgesic pathways response, and then regulates inflammatory response of the immune system [41, 42]. The benefits of Tai chi for KOA have been confirmed, but mostly though self-reported symptoms and function outcomes, ignoring muscle strength and the association with pain and physical function. Our primary therapeutic goal is to examine whether Tai Chi can increase quadriceps strength, thereby reducing pain levels, improving physical function and slowing KOA progression.

While the purpose of this trial is to address the limitations of previous trials, potential challenges remain to be addressed. First, to ensure the successful implementation of the protocol, all researchers are trained prior to the start of the trial and are prepared to properly treat patients through systematic research and detailed protocols. Secondly, to increase the representativeness of the sample, public recruitment will be carried out through posters, social platforms and other forms. Third, to improve the accuracy of the exercise, 8-form Tai Chi is adopted for the elderly, which is easy to understand and beneficial for physical conditions without excessive stress on the joints. Participants will be instructed by Tai Chi instructor with extensive experience and reminded of the forms by pre-recorded videos. Fourth, to achieve patient compliance and minimal follow-up loss, We have successful recruitment experience in our previous research with KOA with a low dropout rate. We will use the following strategies. Clinical trial publicity materials are distributed to all researchers to popularize clinical trial knowledge. Before assigning informed consent, participants should be explained in detail what to look for, including intervention requirements, timelines, positive impacts, and potential adverse events. In addition, we will strengthen KOA medical education, care for patients, and improve the overall quality of life of patients. Participants will receive an adequate transportation allowance if they complete all treatment and follow-up. More importantly, more flexible methods will be used to measure patients during follow-up, such as telephone questions or electronic CRF production through information or other communication software.

TC is easy to learn and self-administered and is not limited by time or space. If TC can improve clinical symptoms in KOA patients, we should promote it in the community in the future. The findings will help determine whether TC is superior to regarding effects on knee pain, physical function and muscle weakness in people with KOA and explore its correlation between pain intensity and muscle strength.

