## Methods/design

### Study design

This is a single-center, evaluator-blind, randomized controlled trial conducted at Shanghai Municipal Hospital of Traditional Chinese Medicine in China. All eligible participants will be randomly divided at a ratio of 1:1 into Tai Chi group (TC group) (1x/week for 12 weeks) and attention control group (AC group) with health education and stretching program (1x/week for 12 weeks) with a follow-up period of 6 weeks. The primary outcome is the change of Western Ontario and McMaster Universities (WOMAC) pain subscale at week 12 compared with baseline. Secondary outcomes include WOMAC pain subscales at other time-points, stiffness and function subscales, data from isokinetic dynamometry, gait analysis with electromyography (EMG), and a 36-item short form health survey (SF-36). The daily dose of pain-relieving medication will also be recorded. All outcomes will be assessed at baseline (week − 1) and at the end of the intervention (week 12). In addition, WOMAC and SF-36 will also be assessed at 6^th^ week of the intervention (week 6) and at the end of follow-up (week 18). The design of this clinical trial will strictly follow the Consolidated Standards of Reporting Trials (CONSORT) Statement and Standard Protocol Items: Recommendations for Interventional Trials (SPIRIT) [30]. The trial flowchart is presented in Fig. 1, and the study design schedule is shown in Table 1; Fig. 1.

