### Inclusion criteria

Meet the diagnostic criteria of KOA set by the American College of Rheumatology [24];Male or female patients aged 40 years or older;Mild to moderate radiographic medial tibiofemoral osteoarthritis (Kellgren - Lawrence score from 1 to 3) in at least one knee;WOMAC pain score ≥ 40 (visual analog version, range 0 to 100, higher indicating more pain) on at least one of five questions;Volunteer to participate in the trial and provide written informed consent.

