### Outcome measurement

#### Primary outcome

The primary outcome is the change in WOMAC pain subscale between baseline and week 12. The self-reported WOMAC pain subscale is aimed to assess pain intensity when walking on a flat surface, going up or down stairs, lying in bed at night, sitting or lying, and standing upright [31]. WOMAC has three subscales evaluating joint pain (score range, 0-500), stiffness (0-200) and physical function (0-1700), respectively, with higher scores indicating more severe disease. The visual analogue scale (VAS) version of WOMAC is a disease-specific, self-administered instrument and widely used in clinical trials with satisfactory reliability and validity [32–34].

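### Week-18 WOMAC may be collected by telephone, although the protocol's WOMAC is a self-completed visual analogue form

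*Protocol article*

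**What the plan says.** Under Primary outcome, the instrument is fixed: "The visual analogue scale (VAS) version of WOMAC is a disease-specific, self-administered instrument". The same section gives the ranges as "joint pain (score range, 0-500), stiffness (0-200) and physical function (0-1700"). The Inclusion criteria use the same format item by item: "visual analog version, range 0 to 100, higher indicating more pain".

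Study design describes 12 weeks of intervention "with a follow-up period of 6 weeks", with WOMAC and SF-36 taken again "at the end of follow-up (week 18"). In Table 1 the Follow-up heading covers week 18 alone. Six items are marked there: WOMAC pain, stiffness and physical function, SF-36, analgesic dose and adverse events. The Secondary outcome section lists the week-18 WOMAC subscales among the secondary outcomes.

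Among its measures to limit loss to follow-up, the Discussion states that "more flexible methods will be used to measure patients during follow-up, such as telephone questions or electronic CRF production". The sentence exempts no outcome.

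**The concern.** A visual analogue item is answered by marking a line. Over the telephone the participant has to speak a number, and an interviewer writes it down. The response is then neither visual analogue nor self-administered, so it is not the instrument the protocol defines. The wording and items of the questionnaire are the same, but the response format and the setting differ.

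Three things are at stake at week 18. First, change from baseline would subtract a mark on a line from a spoken rating for some or all participants. Second, if telephone use is concentrated at week 18, mode is confounded with visit, and a claim that benefit persists or fades after week 12 cannot be separated from a change of format. Third, participants know their allocation (Blinding section). If those who are hard to bring back are the ones telephoned, the share telephoned could differ between arms. The mixed model described under Data collection and statistical analysis has group and visit as fixed effects and would not see this.

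**Working it through.** The conflict itself needs no arithmetic; it follows from four places in the article.

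1. Primary outcome and Inclusion criteria: WOMAC is the visual analogue version, 0 to 100 per item, self-administered. Five pain items give 5 × 100 = 500, which matches the stated pain range, so both sections describe the same format.
2. Study design and Table 1: follow-up is the period from week 12 to week 18, and the only follow-up assessment is week 18.
3. Table 1: three of the six items collected at that assessment are WOMAC subscales. Dynamometry and gait analysis are not repeated, so nothing at week 18 forces attendance.
4. Discussion: telephone questions or an electronic CRF are to be used for measurement in follow-up, with no item excepted.

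Points 1 and 4 cannot both hold for a WOMAC taken by telephone. They can both hold for an electronic form that keeps the line.

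**Possible size.** The documents give no mode effect and no expected share of telephone assessments, so the figures below are assumptions. If telephone scores differ from visual analogue scores by *b* points on 0-500, and the telephone shares in the two arms are *p*₁ and *p*₂, the week-18 group difference in pain shifts by (*p*₁ − *p*₂) × *b*.

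- *b* = 10 to 30 and a gap of 10 to 30 percentage points: 0.10 × 10 = 1 point, up to 0.30 × 30 = 9 points.
- *b* = 25 to 50 (5 to 10 per item over five items) and shares of 40% against 20%: 0.20 × 25 = 5 points, up to 0.20 × 50 = 10 points.
- Equal shares: zero bias in the group contrast for a constant *b*. The change over time within each arm still moves by the common share times *b*; if everyone is telephoned, that is the whole of *b*.

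**Yardstick.** The sample size section gives a 118-point difference, 40 per group, 90% power and two-sided 0.05, but no SD. The implied SD is 118 / [(1.960 + 1.282) × √(2/40)] ≈ 163 by the normal approximation, or about 161 with a t-test. The standard error of a group difference is then about 161 × √(2/40) ≈ 36 points. A shift of 1 to 10 points is about 0.03 to 0.28 standard errors. The 118 points is a week-12 hypothesis, so it serves here only to set a scale.

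**Noise.** A constant shift *b* applied to a share *p* adds variance *p*(1 − *p*)*b*². In the heaviest case tried, *p* = 0.5 and *b* = 50, this adds 0.25 × 2,500 = 625, and the SD goes from 162.8 to √(162.8² + 625) ≈ 164.7. Power on the planning assumptions falls from 90% to about 89.3%. Random error from the spoken format would come on top and cannot be sized from the documents.

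**The case against.** The best case for leaving the text alone has four parts.

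*The sentence does not say that WOMAC is taken by telephone.* Analgesic dose, adverse events and SF-36 are also due at week 18 and need no line, and an electronic CRF is offered as an alternative. This stands in part: the electronic route is compatible with the instrument. But the sentence speaks of measuring patients in follow-up without exception, and half of what is measured then is WOMAC. This is a conflict between two statements in the article, so it is more than detail left to a fuller document.

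*The primary outcome is safe.* This stands. A reader might infer that the week-12 primary could also be taken by telephone. The documents do not support that: follow-up is defined as the six weeks ending at week 18, Table 1 puts week 12 under Intervention, and week 12 also requires dynamometry and gait analysis on laboratory equipment.

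*Differential use by arm is not stated.* This also stands. A reader might infer that telephone use will differ between arms and so bias the contrast. The text does not say who would be telephoned. It could mean everyone at week 18, and the two arms have matched weekly contact and home practice. A differential is possible because allocation is known, but it is not established.

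*The effect is small.* On the assumed figures it is a fraction of a standard error. That is a fair reason for modest priority. It does not remove the confounding of mode with visit, which arises even when both arms are treated alike.

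The route to unblinding through an interviewer adds little, since participants are unblinded and rate their own pain in any mode.

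**Conclusion.** The concern holds for week 18 and for secondary outcomes only. As written, the Discussion permits telephone collection of a questionnaire whose defined format cannot be answered by telephone. Week-18 change in WOMAC pain, stiffness and function may therefore combine two response formats.

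Certain consequences depend on how the telephone is used: some added noise if modes are mixed, and confounding of mode with visit if telephone use is concentrated at week 18. Bias in the group contrast arises only if telephone shares differ between arms, or if the mode effect itself does. The 1 to 10 points given above rest wholly on assumed mode shifts and shares, so the true size is unknown. This is a cheap improvement, and it is better made early: recruitment has begun, and a mode that was never recorded cannot be recovered at analysis.

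**What to change.** - Amend the Discussion sentence so that any remote WOMAC at week 18 uses the same self-completed visual analogue scale in electronic form, by link or through the WeChat mini-app already in use. Provide a mailed paper form for participants who cannot use it.
- Limit telephone questions to items that need no visual line, such as medication dose and adverse events, and to reminders. Telephone contact should not be dropped altogether: a participant lost for want of a call would have the week-12 score carried forward to week 18 under the planned LOCF.
- Record the mode of every WOMAC assessment on the CRF.
- If modes differ, add a sensitivity analysis of the week-18 contrast that accounts for mode, for example by shifting the scores taken in another mode over a plausible range and re-estimating. Simply excluding remote assessments would select on a variable that arises after randomisation and could create the bias it is meant to detect.

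The cost is a wording change, a small electronic form, one CRF field, and possibly a few missing week-18 scores among participants who return neither form.

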### Trial status

At the time of submission, recruitment for the trial has been started. Te first participant was included on 25 April 2023.

## Data Availability

Not applicable.

## Abbreviations

AC: Attention Control
AEs: Adverse Events
ANOVA: Analysis of Variance
AP: Average Power
BP: Bodily Pain
CONSORT: Consolidated Standards of Reporting Trials
CRF: Case Report Form
EMG: Electromyography
GH: General Health
IQR: Interquartile Range
KOA: Knee Osteoarthritis
LOCF: Last Observation Carried Forward
MH: Mental Health
MVC: Maximal Voluntary Contraction
NSAIDS: Nonsteroidal Anti-inflammatory Drugs
PF: Physical Functioning
PPS: Per-Protocol Set
PT: Peak Torque
PTA: Peak Torque Angle
PW: Peak Work
RE: Role Limitations due to Emotional Problems
RP: Role Limitations due to Physical Problems
SAE: Severe Adverse Event
SF: Social Functioning
SF-36: 36-item Short Form Health Survey
SPIRIT: Standard Protocol Items:Recommendations for Interventional Trials
TC: Tai Chi
TESS: Treatment Emergent Symptom Scale
VT: Vitality
TW: Total Work
WOMAC: Western Ontario and McMaster Universities
